## Stillbirth

|                   |
|-------------------|
| STILLBIRTH |
|-------------------|

Stillbirth is defined as a fetal death occurring before birth after a selected, predefined duration of gestation. The death of the fetus could have occurred before the onset of labor (ante partum) or at the time delivery (intra partum).

| Newborn case number                        |                                                                                                                      |                                                                                                                                                                                                                                                                                      |
|--------------------------------------------|----------------------------------------------------------------------------------------------------------------------|--------------------------------------------------------------------------------------------------------------------------------------------------------------------------------------------------------------------------------------------------------------------------------------|
| QUESTION                                   | ANSWERS                                                                                                              |                                                                                                                                                                                                                                                                                      |
| PART 1 - STILLBIRTH                 |                                                                                                                      |                                                                                                                                                                                                                                                                                      |
| A Birth                             |                                                                                                                      |                                                                                                                                                                                                                                                                                      |
| 1                                          | What was the date of delivery?
(If 'no' or 'unknown' skip to section C)                                           | Please enter DDMMYYYY or unknown.                                                                                                                                                                                                                                                    |
| 2                                          | Was the delivery attended?
(If 'no' or 'unknown' skip to section C)                                               | Yes
No
Unknown                                                                                                                                                                                                                                                                 |
| 3                                          | Who attended the delivery?                                                                                           | Midwife
Obstetrician
Matern-fetal medicine specialist
Other, please specify
Unknown                                                                                                                                                                                      |
| C Absence of signs of life at birth |                                                                                                                      |                                                                                                                                                                                                                                                                                      |
| 4a                                         | Was a physical examination of the fetus/infant performed after delivery?
(If 'no' or 'unknown' skip to section D) | Yes
No
Unknown                                                                                                                                                                                                                                                                 |
| 4b                                         | By whom was the physical examination performed?                                                                      | General practice physician
Matern-fetal medicine specialist
Midwife
Neonatologist
Nurse practitioner
Obstetrician
Pathologist
Pediatrician
Physician's assistant
Other qualified trained practitioner, please specify
Other, please specify
Unknown |
| 5                                          | Indicate among the following signs, which were present at birth                                                      |                                                                                                                                                                                                                                                                                      |
| 5a                                         | Sign of life (unspecified)                                                                                           | Yes
No
Unknown                                                                                                                                                                                                                                                                 |
| 5b                                         | Spontaneous movement                                                                                                 | Yes
No
Unknown                                                                                                                                                                                                                                                                 |

|                                                                                       |                                                                                                                                        |                      |
|---------------------------------------------------------------------------------------|----------------------------------------------------------------------------------------------------------------------------------------|----------------------|
| 5c                                                                                    | Umbilical cord pulse                                                                                                                   | Yes
No
Unknown |
| 5d                                                                                    | Heartbeat                                                                                                                              | Yes
No
Unknown |
| 5e                                                                                    | Respiration/spontaneous respiration                                                                                                    | Yes
No
Unknown |
| 5f                                                                                    | Crying                                                                                                                                 | Yes
No
Unknown |
| 6                                                                                     | Was the Apgar score 0 at 1 and 5 minutes?                                                                                              | Yes
No
Unknown |
| 7                                                                                     | Was there whole body cyanosis?                                                                                                         | Yes
No
Unknown |
| 8                                                                                     | Was there response to resuscitation?                                                                                                   | Yes
No
Unknown |
| 9a                                                                                    | Was the physical examination after birth consistent with antepartum death? (e.g. maceration, meconium staining, tissue injury, oedema) | Yes
No
Unknown |
| 9b                                                                                    | Was the physical examination after birth consistent with intrapartum death?                                                            | Yes
No
Unknown |
| E Pathology report                                                             |                                                                                                                                        |                      |
| 10                                                                                    | Was a fetal/placental pathology report available?
(If 'no' or 'unknown' skip to section F)                                          | Yes
No
Unknown |
| 11                                                                                    | Was this consistent with antepartum death?                                                                                             | Yes
No
Unknown |
| F Presence of fetal heart tones and fetal movement prior to the onset of labor |                                                                                                                                        |                      |
| 12a                                                                                   | Was there a prenatal ultrasound examination ?
(If 'no' or 'unknown' skip to question 13a)                                           | Yes
No
Unknown |
| 12b                                                                                   | Did the prenatal ultrasound examination document fetal heart tones before the onset of labor?                                          | Yes
No
Unknown |
| 12c                                                                                   | Did the prenatal ultrasound examination document fetal movement before the onset of labor?                                             | Yes
No
Unknown |
| 13a                                                                                   | Was auscultation for fetal heart tones performed prior to the onset of labor?                                                          | Yes
No            |

|                                               |                                                                                                                                                 |                                        |
|-----------------------------------------------|-------------------------------------------------------------------------------------------------------------------------------------------------|----------------------------------------|
|                                               | (If 'no' or 'unknown' skip to question 14a)                                                                                              | Unknown                                |
| 13b                                           | Were fetal heart tones documented by auscultation prior to the onset of labor?                                                                  | Yes
No
Unknown                   |
| 14a                                           | Was a hand held Doppler used for fetal heart tones performed prior to the onset of labor?
(If 'no' or 'unknown' skip to question 15a) | Yes
No
Unknown                   |
| 14b                                           | Were fetal heart tones document by a hand held Doppler prior to the onset of labor?                                                             | Yes
No
Unknown                   |
| 15a                                           | Does the medical record state the mother reported fetal movement prior to onset of labor?                                                       | Yes
No
Unknown                   |
| 15b                                           | Does the medical record state the mother reported a lack of fetal movement for 24 hours of more prior to the onset of labor?                    | Yes
No
Unknown                   |
| 15c                                           | Did a physical examination of the mother confirm lack of fetal movement?                                                                        | Yes
No
Unknown                   |
| 16                                            | Are radiology findings consistent with intrauterine fetal death?                                                                                | Yes
No
Unknown
Not applicable |
| PART 2 - GESTATIONAL AGE AT STILLBIRTH |                                                                                                                                                 |                                        |
| 17                                            | Please see Reference CRF GA                                                                                                                     |                                        |

### Low birth weight

|                                            |                                       |
|--------------------------------------------|---------------------------------------|
| LOW BIRTH WEIGHT                    |                                       |
| Low birth weight is defined as <2500 grams |                                       |
| PART 1 - GESTATIONAL AGE AT BIRTH   |                                       |
| 1                                          | Please see Reference CRF BIRTH WEIGHT |

### Small for gestational age

|                                  |
|----------------------------------|
| SMALL FOR GESTATIONAL AGE |
|----------------------------------|

Small for gestational age is defined as a birth weight for gestational age below the 10th percentile based on a sex-specific reference population (WHO, 1995)

| Newborn case number                                                                                                                         |                      |
|---------------------------------------------------------------------------------------------------------------------------------------------|----------------------|
| QUESTION                                                                                                                                    | ANSWERS              |
| PART 1 - GA                                                                                                                          |                      |
| 1 Please see Reference CRF GA                                                                                                               |                      |
| PART 2 - BIRTH WEIGHT                                                                                                                |                      |
| H Birth weight of the newborn                                                                                                               |                      |
| 2 Please see Reference CRF birth weight                                                                                                     |                      |
| PART 3 - SGA                                                                                                                         |                      |
| 3 Was GA assessed only by infant examination?                                                                                               | Yes
No
Unknown |
| 4 Was the baby noted to be small, but no actual weight recorded?                                                                            | Yes
No
Unknown |
| 5 Was the diagnosis of small for gestational age extracted from billing codes or chart, with no documentation of actual birth weight or GA? | Yes
No
Unknown |

### Congenital microcephaly (post-natally diagnosed)

#### POST NATALLY DIAGNOSED CONGENITAL MICROCEPHALLY

Small for gestational age is defined as a birth weight for gestational age below the 10th percentile based on a sex-specific reference population (WHO, 1995)

| Newborn case number                                                             |                                                                                     |
|---------------------------------------------------------------------------------|-------------------------------------------------------------------------------------|
| QUESTION                                                                        | INSTRUCTIONS                                                                        |
| PART 1 - GA and sex                                                      |                                                                                     |
| 1 Did a live birth, stillbirth, or spontaneous/therapeutic abortion take place? | Live birth
Stillbirth
Spontaneous abortion
Therapeutic abortion
Unknown |
| 2 What is the sex of the baby?                                                  | Male                                                                                |

|                                         |                                                                                                                                                                 |                                                                                                                                                                                                                                                                       |
|-----------------------------------------|-----------------------------------------------------------------------------------------------------------------------------------------------------------------|-----------------------------------------------------------------------------------------------------------------------------------------------------------------------------------------------------------------------------------------------------------------------|
|                                         |                                                                                                                                                                 | Female
Unknown                                                                                                                                                                                                                                                     |
| 3                                       | Please see Reference CRF GA                                                                                                                                     |                                                                                                                                                                                                                                                                       |
| PART 2 - Congenital microcephaly |                                                                                                                                                                 |                                                                                                                                                                                                                                                                       |
| 1                                       | Was the head circumference measured and recorded?
If 'no' or 'unknown' skip question 5.                                                               | Yes
No
Unknown                                                                                                                                                                                                                                                  |
| 2a                                      | What was the head circumference?                                                                                                                                | Please enter a number.                                                                                                                                                                                                                                         |
| 2b                                      | What are the units of the head circumference measurement?                                                                                                       | Centimeters
Inches
Other, please specify
Unknown                                                                                                                                                                                                             |
| 4                                       | When was the head circumference measured?                                                                                                                       | Within the first 24h (take into account the variability in this period based on molding of the head)
24-36h after birth or end of pregnancy
>36h and up to 6 weeks after birth or end of pregnancy with no apparent post-natal insult resulting in microcephaly |
| 5a                                      | Was there any diagnosis of congenital microcephaly using codes ICD-9-CM code 742.1 or ICD-10-CM code Q02?
If 'no' or 'unknown' skip to last question. | Yes
No
Unknown                                                                                                                                                                                                                                                  |
| 5b                                      | Was there an inpatient diagnosis of congenital microcephaly using ICD-9-CM code 742.1 or ICD-10-CM code Q02?                                                    | Yes
No
Unknown                                                                                                                                                                                                                                                  |
| 5c                                      | Were there at least 2 outpatient diagnosis of congenital microcephaly using ICD-9-CM code 742.1 or ICD-10-CM code Q02?                                          | Yes
No
Unknown                                                                                                                                                                                                                                                  |
| 5d                                      | Was there an outpatient diagnosis of congenital microcephaly AND death in the first year using ICD-9-CM code 742.1 or ICD-10-CM code Q02?                       | Yes
No
Unknown                                                                                                                                                                                                                                                  |
| 6                                       | Was congenital microcephaly based on physical inspection without head circumference measurement?                                                                | Yes
No
Unknown                                                                                                                                                                                                                                                  |

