## Annex III. GAIA case definitions

### Congenital microcephaly

#### *Post-natally diagnosed congenital microcephaly*

##### Level 1 of diagnostic certainty

1. Live birth, stillbirth, or spontaneous or therapeutic abortion of at least 24 weeks of Gestational Age (GA)~  
AND
2. HC 2 SD below mean or <3 percentile according to GA and gender, using appropriate standardized reference charts for the population (e.g., WHO growth reference charts if GA ≥37 weeks and Intergrowth-21st reference charts for GA 24–36 weeks)  
AND
3. Measured between 24 and 36 h after birth or end of pregnancy.

~GA assessed based on certain LMP with confirmatory 1st trimester or 2nd trimester US scan, IUI, or embryo transfer date.

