##### Level 2A of diagnostic certainty

1. Live birth, stillbirth, or spontaneous or therapeutic abortion of at least 24 weeks of GA~  
AND
2. HC 2 SD below mean or <3 percentile according to GA and gender, using appropriate standardized reference charts for the population (e.g., WHO growth reference charts if GA ≥37 weeks and Intergrowth-21st reference charts for GA 24–36 weeks)  
AND
3. Measured within the first 24 h § OR Measured >36 h and up to 6 weeks after birth or end of pregnancy with no apparent post-natal insult resulting in microcephaly

~GA assessed based on certain LMP with confirmatory 1st trimester or 2nd trimester US scan, IUI, or embryo transfer date

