#### Level 3A of diagnostic certainty

1. Live birth, stillbirth, or spontaneous or therapeutic abortion of at least 24 weeks of GA~  
AND
2. HC 2 SD below mean or <3 percentile according to GA and gender, using appropriate standardized reference charts for the population (e.g., WHO growth reference charts if GA ≥37 weeks and Intergrowth-21st reference charts for GA 24–36 weeks)  
AND
3. Measured up to 6 weeks after birth or end of pregnancy with no apparent post-natal insult resulting in microcephaly

~GA based on LMP without confirmatory 1st or 2nd trimester ultrasound

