### Reference CRF: birth weight

| QUESTION                     |                              | ANSWERS                                  |
|------------------------------|------------------------------|------------------------------------------|
| PART 1 – BIRTH WEIGHT |                              |                                          |
| A                     | Birth                 |                                          |
| 1                            | Date of birth of the newborn | Please enter DDMMYYYY or unknown. |
| B                     | Weight                |                                          |

|              |                                                                                       |                                                                                                    |
|--------------|---------------------------------------------------------------------------------------|----------------------------------------------------------------------------------------------------|
| 1            | Was the newborn weighed?
If 'no' or 'unknown' skip to B4..                  | Yes
No
Unknown                                                                               |
| 2a           | What was the weight of the newborn infant?
If 'unknown' skip to question 3. | Please enter a number.                                                                      |
| 2b           | What are the units of the weight measurement?                                         | Grams
Kilograms
Pounds
Other, please specify
Unknown                                   |
| 3            | Was the weight category assessed as <2500g?                                           | Yes
No
Unknown                                                                               |
| 4            | Was a proxy measure of birth weight used?                                             | Yes, please specify
No
Unknown                                                               |
| 5            | When was the newborn infant weighed?                                                  | Within 24 hours of birth
On day 1 or 2 of life (first 48 hours)
On day 3 or after
Unknown |

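### The head circumference timing item on the microcephaly CRF has no true answer for a late measurement with an apparent insult, or for an unrecorded time

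*Protocol*

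**What the plan says.** Annex V, post-natally diagnosed congenital microcephaly, Part 2, item 4 asks "When was the head circumference measured" and gives three answers:

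- within the first 24 hours, with a caution about molding of the head;
- from 24 to 36 hours, with no statement about an insult;
- a late category, worded ">36h and up to 6 weeks after birth or end of pregnancy with no apparent post-natal insult resulting in microcephaly".

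Nothing follows the third answer. No other CRF item shown asks about a post-natal insult or records when head circumference was taken. The delivery register (sections 4.6 and 4.9) adds head circumference but not its timing.

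Annex III uses these facts to assign levels. Level 1 needs "Measured between 24 and 36 h after birth or end of pregnancy". Levels 2A and 2B accept a measurement in the first 24 hours or, in the wording of 2A, "Measured >36 h and up to 6 weeks after birth or end of pregnancy with no apparent post-natal insult resulting in microcephaly". Level 3A needs "Measured up to 6 weeks after birth or end of pregnancy with no apparent post-natal insult resulting in microcephaly".

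Levels are assigned by an automated tool (section 4.10), and data are analysed as recorded, without imputation (section 5.5).

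**The concern.** The third answer carries the late-measurement wording of Levels 2A and 2B into a response list. What the definition treats as a condition to be checked becomes something asserted by whoever reports a late measurement. With no unknown option, the same list also assumes that the time is always on record, although section 4.1 reports sites' concern that data may go unrecorded or be irretrievable.

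The results at stake are a primary outcome (applicability, section 5.2.2.1), a secondary outcome (proportions by level, section 5.3.1.1) and the exploratory tables meant to show which missing elements block classification (sections 5.4.1 and 5.4.2). The EDC is to be built on the CRFs (section 8.2), so the response list carries into the live tool, and no analysis plan can recover a fact that the form did not capture.

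**Working it through.** There is no figure in the plan to reproduce. The check is to take each situation that can arise and ask whether item 4 offers a true answer, and what Annex III then does with the entry.

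| Situation | True answer available? | Effect of a tick | Effect of a blank |
|---|---|---|---|
| (a) Up to 36 h, time known | Yes, first or second answer | Timing correct; insult not recorded, though Level 3A requires it | Not applicable |
| (b) After 36 h, record shows no insult | Yes, third answer | Correct | Not applicable |
| (c) After 36 h, apparent insult | No | Third answer wrongly meets the criterion of 2A, 2B or 3A | Not classified on head circumference, which is right, but the reason is not coded |
| (d) After 36 h, record silent on insult | Arguably the third answer | Defensible, but cannot be separated from (b) | Reason not coded |
| (e) Time not recorded | No | Any tick asserts a time; the second answer meets the Level 1 timing criterion | Timing not shown for 1, 2A, 2B or 3A; reason not coded |

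Three points follow.

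1. *How much item 4 decides.* In Annex III, Levels 1 and 2A carry the same head circumference criterion and the same gestational age basis (certain LMP with a confirmatory first- or second-trimester scan, insemination date or embryo transfer date). Only criterion 3, the time of measurement with its insult condition, separates them. For infants with that basis, item 4 alone decides between the two levels.

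2. *Level 3A.* An infant whose gestational age rests on LMP without a confirmatory scan can reach only 3A among the levels that use head circumference. If measured in the first 36 hours, the infant gets a truthful first or second answer, but the no-insult condition is left unrecorded. The classification must then ignore the condition or assume it.

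3. *Comparison with similar items.* Items 1, 2b, 5a to 5d and 6 of the same part offer an unknown option. The corresponding timing item in the birth weight reference CRF closes its list with two answers, "On day 3 or after Unknown": an unconditional late category and an unknown option. Item 4 has neither.

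*Weight of one case.* Section 5.1.2 aims for 100 cases per outcome per site. One case that becomes classified, or fails to be, because of item 4 moves site applicability by 1/100 = 1 percentage point. At 25 cases, the lowest count in the 50% column of Table 1, it moves it by 1/25 = 4 points. If the infant would be classified anyway through a code, only the level distribution changes.

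**The case against.** Several stronger readings are tempting, and the documents do not support them.

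- *That staff are forced into a false entry.* Nothing says item 4 is mandatory. Section 8.1 provides feedback on missing fields, manual review and queries, and section 4.8 requires entries to rest on source documents. An unknown time entered as 24-36 hours would breach that rule.
- *That a false tick and a blank cannot be told apart.* They plainly can. What cannot be recovered is the reason for a blank, or whether a given tick is true.
- *That affected infants are lost.* A coded diagnosis can still give Level 3B or 4 (items 5a to 5d), and Level 4 also admits diagnosis by inspection where no measurement was made. For a real insult after 36 hours, failing the levels based on head circumference is the correct result.
- *That an unrecorded insult status is a false entry.* The definition asks only that no insult be apparent, and a record that shows none can meet it. Requiring documented absence could be stricter than the definition under test and bias applicability downward.
- *That an unknown time can by itself earn Level 1.* The head circumference and gestational age criteria must also be met.
- *That item 4 is the only item without an unknown option.* Item 2a, the numeric value, has none either.

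The item numbering also jumps from 2b to 4, so an item may have been dropped or lost when the PDF was read. The completion guidelines, manual of procedures and eCRF skip logic are not shown and might govern how item 4 is answered. A blank would still be counted as missing under sections 5.4 and 5.5, so the gap is partly visible.

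All of this narrows the point. None of it supplies a true answer for situations (c) and (e), or records insult status for Level 3A.

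**Conclusion.** The point holds in a limited form. As shown, item 4 has no true answer for a measurement after 36 hours with an apparent insult, nor for one whose time is unrecorded. An untrue tick can meet a Level 1, 2A, 2B or 3A criterion; a blank hides why the case was not classified. In addition, the no-insult condition of Level 3A is not captured for measurements in the first 36 hours.

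The number of infants affected cannot be derived from the documents, which give neither the share measured late nor the frequency of insults or unrecorded times. A reader might want a percentage; none can be supported. The effect is confined to one of seven health outcomes and does not threaten the study as a whole. It does touch a primary outcome and the tables meant to explain non-classification, and it is cheap to repair. The conclusion assumes that the printed form is complete and that no unseen instruction provides the missing options.

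**What to change.** Replace item 4 with two items:

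1. Time of head circumference measurement: within 24 h / 24-36 h / more than 36 h to 6 weeks / unknown.
2. Apparent post-natal insult that could explain the microcephaly: yes / no / not recorded.

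Then state the classification rules:

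- Do not grant Level 2A or 2B through the late window, or Level 3A, when item 2 is yes.
- Report infants with item 2 not recorded separately, and show applicability with and without them, because the definition asks only for no apparent insult.
- List unknown time of measurement as a missing element in section 5.4.

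The cost is one added CRF item, an EDC update, and a re-query of the microcephaly cases already entered.
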